##### Sleep

Insomnia complaints are assessed by the Insomnia Severity Index (ISI; [198]). The ISI contains seven items that are scored on a five point Likert scale. The ISI has shown to be a valid measure in community and insomnia patient samples [198], although the reliability was questionable in some studies (e.g., [199, 200]). In addition to insomnia, the number of nights with nightmares and the total number of nightmares in the week prior to the assessment are measured using the Nightmare Frequency Questionnaire (NFQ; [201]). Based on previous research among posttraumatic stress disorder (PTSD) patients, the NFQ appears reliable for measuring nightmare frequency [201].

##### Well-being

Well-being is measured using a single item measuring happiness [202] and the Outcome Rating Scale (ORS; [203]). The single item measures general happiness in the months prior to the assessment on a seven point Likert scale. Reliability and validity were good among undergraduates [202], and sensitivity to change was excellent in a BPD sample [184]. The ORS consists of four VAS items assessing four areas of functioning: individual (personal well-being), interpersonal (family and close relationships), social (work and/or school functioning), and overall (general sense of well-being). We slightly adapted the third dimension of the ORS by excluding friendships, because of its overlap with the second dimension (interpersonal functioning). Hafkenscheid et al. [204] reported adequate psychometric properties of the ORS is a Dutch outpatient sample.

### Statistical analyses

The statistical analyses for the (cost-)effectiveness, mechanisms of change and treatment selection studies are under development. For example, according to Cohen et al. [48], the treatment selection field is still in its developmental stage and statistical methods are constantly evolving. Recently, great efforts have been made by several authors (e.g., [205, 206]) to select the optimal prediction model by comparing different variable selection techniques. Considering the ongoing advances in methodological approaches, the statistical analyses described below should be considered as examples of appropriate analytic methods. We will determine the optimal methods at the time of the analyses. An update of the protocol will be published, including the selected statistical methods, before start of the data-analyses. The statistical analyses will be performed according to the intention-to-treat (ITT) principle (i.e., including all patients that have been randomized and received at least one treatment session). In addition to the primary analysis based on the ITT principle, a completers analysis will be conducted by excluding patients who dropped out prematurely (i.e., termination of the treatment before planned end, without patient and therapist agreeing that enough improvement has been reached to justify the termination) or deviated from the protocol (e.g., sought other psychological treatment in addition to the study treatment). No interim analyses are planned.

#### Treatment selection

A two-step approach will be applied to determine the optimal treatment for a particular patient by identifying patient characteristics that predict (differential) treatment response. First, we will examine which of the candidate predictors (see Additional file 4 for an overview) predict (differential) treatment response. Many different variable selection approaches can be used to identify which of the candidate predictors contribute to the prediction of treatment outcome, for example elastic net regularization [207], Bayesian additive regression trees [208], or a combination between different variables selection procedures [48]. Second, individual treatment recommendations are generated based on a prediction model including the variables that predict (differential) treatment response. For each patient, the most beneficial treatment will be identified by using the prediction model to estimate the predicted outcomes for both treatments including the difference in predicted outcomes.

Our primary analysis will focus on individual treatment recommendations based on change in BPD manifestations and will therefore reveal the advantage in symptom relief that may be gained if patients are allocated to their predicted optimal treatment compared to their predicted non-optimal treatment. To investigate the advantage that may be gained in other outcomes, such as functioning and cost-effectiveness, generalization analyses will be performed by testing the performance of the prediction model for these outcomes.

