Historically, research has focused on a single variable to predict treatment response, but often failed to find consistent and clinically meaningful moderators [41–44]. However, it is highly unlikely that a single variable is responsible for the differences in treatment response [43, 45, 46]. In recent decades, novel approaches combining multiple predictors to determine the optimal treatment for a particular patient have been introduced, including the methods of Kraemer ([47]; optimal composite moderator) and DeRubeis and colleagues ([35]; statistically derived selection algorithm). Several studies have found that a combination of predictors was predictive of differential treatment response (e.g., [48–50]). For example, by using the method of DeRubeis and colleagues, it was investigated in an effectiveness study among BPD patients which of two different treatments (DBT and General Psychiatric Management; GPM) would have been the optimal treatment option for a particular patient in terms of long term outcome [45]. The authors found that BPD patients with childhood emotional abuse, social adjustment problems, and dependent personality traits were more likely to benefit from DBT compared to GPM, whereas GPM excelled for patients with more severe problems related to impulsivity. The authors also provided an estimate of the advantage that might be gained if patients had been allocated to the optimal treatment option. The average difference in outcomes between the predicted optimal treatment and non-optimal treatment for all patients was small-to-medium (*d* = 0.36), while the advantage for patients with a relatively stronger prediction increased to a medium-to-large effect (*d* = 0.61). This suggests that treatment allocation based on a treatment selection procedure may substantially improve outcomes for BPD patients.

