This trial provides a unique opportunity to gain more insight into one of the main questions dominating the psychotherapy research agenda: “What works for whom and why?”. Although DBT and ST share some important characteristics, different interventions related to different assumed core deficits in BPD are provided [58]. As each treatment provides a different therapeutic milieu and focuses on different goals and tasks, a particular treatment may be a better fit with some patients compared to others [45]. In this study, patient characteristics of (differential) treatment response will be identified and individual treatment recommendations (DBT or ST) will be generated. In addition, for each patient, an estimate will be provided of the potential advantage in symptom relief that might be gained in case the patient was allocated to his or her indicated treatment. Moreover, the potential advantage in other outcomes, for example functioning and cost-effectiveness, will also be estimated. Knowing which treatment is most cost-effective for whom may lead to more efficient allocation of healthcare resources, which is important, as the current healthcare system is characterized by constraints in resources (e.g., people, time, budget; [221]). However, before a treatment selection procedure can be implemented in clinical practice, replication and external validation of the prediction model is needed. Subsequently, a prospective study in which the patient and clinician collaborate in selecting the optimal treatment (i.e., shared decision making; [222]), guided by treatment recommendations based on the prediction model, should be conducted to evaluate the advantage of a treatment selection procedure. By using a state-of-the-art approach, the results of the current study can serve as the starting point for future studies into personalized medicine among BPD patients, and is therefore of great importance.

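### The treatment-selection analysis presents predicted-optimal versus predicted-non-optimal treatment as the advantage to be gained; this is twice the gain over 1:1 allocation and includes the treatment main effect

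*Protocol article*

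**What the plan says.** In Statistical analyses, Treatment selection, a prediction model gives each patient a predicted outcome under DBT and under ST. The better treatment is identified "by using the prediction model to estimate the predicted outcomes for both treatments including the difference in predicted outcomes". The section continues: "Our primary analysis will focus on individual treatment recommendations based on change in BPD manifestations", and says this will reveal "the advantage in symptom relief that may be gained if patients are allocated to their predicted optimal treatment compared to their predicted non-optimal treatment". The same model is then tested on other outcomes, such as functioning and cost-effectiveness, to see what advantage may be gained there.

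The Discussion promises each patient an estimate of "the potential advantage in symptom relief that might be gained in case the patient was allocated to his or her indicated treatment", without naming the alternative to that allocation.

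The Background section on treatment selection reports the same kind of contrast from an earlier study of DBT and General Psychiatric Management: "The average difference in outcomes between the predicted optimal treatment and non-optimal treatment for all patients was small-to-medium", with d = 0.36, and d = 0.61 for patients with stronger predictions. It concludes: "This suggests that treatment allocation based on a treatment selection procedure may substantially improve outcomes for BPD patients".

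The article nowhere compares the selection rule with random allocation, with usual allocation, or with one treatment for everyone.

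**The concern.** A selection procedure would replace some existing way of assigning patients. The natural benchmarks are allocation without regard to patient characteristics and giving everyone the treatment that is better on average. Giving every patient the treatment predicted to be worse for that patient is neither. A contrast against it answers a different question from how much a selection procedure would gain.

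Two consequences follow, even for a perfect and externally validated model. The contrast is larger than the gain over either benchmark. It also includes any plain difference between DBT and ST, which needs no model to exploit. Treatment selection is the trial's main aim, and its result is meant to inform later studies of a selection procedure. If V is read as the gain, as the Background reads the earlier study, those studies would be planned on too large a figure.

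**Working it through.** **The plan's own figure.** The article gives no expected value for V. The design figure tied to this objective is 80% power for a moderator of f = .20 with N = 200 and two-sided alpha .05 (Sample size). A noncentral F with 1 numerator df and noncentrality f² × N = 0.04 × 200 = 8 gives 80.4%. It reproduces, but it says nothing about V.

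**Inputs.** The contrast comes from the Treatment selection analysis section. The value 0.36 comes from the Background. The article does not give m, and the Discussion says a hypothesis about it can hardly be formulated. I therefore take m from 0 to 0.50 as an assumption; the upper end is the effect used for power. All values are in SD units, with higher meaning better.

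**Identity.** Let R be the mean outcome if the rule is followed and R' the mean if it is reversed. Each patient receives one treatment under the rule and the other under its reverse, so:

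- R + R' = mean under DBT + mean under ST.
- V = R - R' = 2R - (mean under DBT + mean under ST).
- The mean under 1:1 allocation is half that sum, so the gain over 1:1 is V/2.
- The mean under the better single treatment is half that sum plus |m|/2, so the gain over it is (V - |m|)/2.

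No assumption about the model or its accuracy is used.

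**Applied to V = 0.36:**

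| Assumed m | Gain over 1:1 | Gain over better single treatment |
|---|---|---|
| 0 | 0.18 | 0.18 |
| 0.10 | 0.18 | 0.13 |
| 0.20 | 0.18 | 0.08 |
| 0.30 | 0.18 | 0.03 |
| 0.36 | 0.18 | 0.00 |
| 0.50 | 0.18 | -0.07 |

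The 0.61 refers to a subgroup; within it the gain over 1:1 is 0.61/2 = 0.305.

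**Illustrations from assumed effects:**

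- *m = 0.50, no moderation, everyone recommended the better arm.* V = 0.50. Gain over the better arm (0.50 - 0.50)/2 = 0; over 1:1, 0.25.
- *m = 0.30, SD of individual effects 0.30 (normal), perfect rule.* V is the mean absolute individual effect: 0.30 × 0.798 × exp(-0.5) + 0.30 × 0.683 = 0.145 + 0.205 = 0.35. Gain over the better arm (0.35 - 0.30)/2 = 0.025.
- *m = 0.30, no moderation, prediction noise SD 0.30.* The rule picks the better arm with probability 0.841. V = 0.30 × (2 × 0.841 - 1) = 0.205. Gain over the better arm (0.205 - 0.30)/2 = -0.048; over 1:1, about +0.10.

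**Simulation at this sample size.** N = 200, 20 predictors and a ridge treatment-by-covariate model (both assumed), 400 trials per setting:

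- *m = 0.30, no moderation.* Cross-validated contrast 0.15, true V 0.14, gain over the better arm -0.08. V was positive while the rule did worse than the better arm in 97% of trials.
- *m = 0.30, SD of individual effects 0.40.* True V 0.26, gain -0.02, and the same reversal in 73%.
- *m = 0, no moderation.* True V is 0, but the mean absolute predicted difference is still 0.37.

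The first setting shows that cross-validation can estimate V well without making V the right quantity. The last shows why any estimate of gain also needs data not used to fit the rule.

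**The case against.** Much of the case on the other side stands.

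- *The label is accurate.* The article says openly that it compares predicted optimal with predicted non-optimal treatment. A reader might infer that V is misdescribed or is a confirmatory headline test. The text does not support that: no threshold or success claim is attached to V, and calling the analysis primary mainly ranks BPD manifestations above other outcomes.
- *Methods are provisional.* The analyses are called examples, and an update is promised before data analysis. That makes the change easy, but the contrast itself is stated without an example marker, and no modelling technique alters its comparator.
- *The value of selection is left to later work.* The Discussion asks for replication, external validation and a prospective study. External validation removes neither the factor of two nor the main effect.
- *The main effect is reported anyway.* Comparative effectiveness is a separate objective, so a reader holding V and m could compute (V - |m|)/2. Nothing in the article tells the reader to do so.
- *For one patient choosing between two treatments, the alternative is the other treatment.* This is fair, and it is a reason to keep the contrast as a descriptive figure. It does not make V the gain from a procedure applied to all patients.

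Two stronger readings are tempting. One is that V is always at least twice the real gain. That holds against 1:1 allocation, the better single treatment, or any allocation that matches patients no worse than chance. If everyone would otherwise receive the poorer treatment, the gain is (V + |m|)/2, and the article does not say how patients are now allocated. The other is that a positive V can hide harm outright. It can do so only relative to the better arm for all, and only if m is not zero; against 1:1 a truly positive V is always a gain. The limitations allow that differential effects may be small or absent, and at m = 0 both gains equal V/2.

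**Conclusion.** The concern holds as a poorly chosen comparator, not as a false statement. The factor of two against 1:1 allocation is exact for every rule. Against the better single treatment, V overstates the gain by a factor of 2/(1 - |m|/V) when V exceeds |m|: for V = 0.36 this is 2.0 at m = 0, 4.5 at m = 0.20 and 12 at m = 0.30. The sign reverses when 0 < V < |m|.

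How much this matters depends on m and on the spread of individual effects, neither of which the article gives. The simulated frequencies depend further on an assumed model and number of predictors, so they show that a reversal is plausible at N = 200 and do not forecast it. The Background shows that the misreading is a live risk, because it takes d = 0.36 on this contrast as a sign of substantial improvement; against 1:1 allocation that figure is 0.18. This should be fixed, but it does not undermine the design.

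**What to change.** In the announced protocol update, report two estimates of the gain from selection: (a) mean outcome under the rule minus mean outcome if all received the on-average better treatment, and (b) mean outcome under the rule minus mean outcome under 1:1 allocation. Give each a confidence interval. Estimate both by cross-validation or in data not used to fit the rule, weighting by each patient's recorded allocation probability, because the Randomization section allows unequal ratios and an alternative method.

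Keep optimal versus non-optimal as a descriptive figure and do not describe it as the gain from a selection procedure. State the comparator in the Discussion wherever an advantage is promised. No significance gate is needed, since the objective is model development and the limitations concede a small sample for it.

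The cost is a little more analysis and a reported gain at most half as large as V. No extra data are required.

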#### Mechanisms of change

It is hypothesized that the treatments exert a remedial effect on the frequency and severity of BPD manifestations by their impact on the BPD-treatment-specific (ST: beliefs and schema modes; DBT: emotion regulation and skills use), BPD-treatment-generic (therapeutic environment characterized by genuineness, safety, and equality), and non-specific (attachment and therapeutic alliance) mechanisms of change. Since potential mediators and outcome will be assessed multiple times, temporal patterns of change can be studied by performing mediation analysis for longitudinal data, for example multilevel autoregressive mediation analysis [209] or multilevel structural equation modeling [210]. By using advanced statistical models, the hierarchical structure of the data (repeated measures nested within patients, who in turn are nested within centers) can be taken into account and possible concurrent and temporal relations between mediators and outcome can be investigated.

#### Clinical effectiveness

Change in the outcome measures and the relative effectiveness of the two treatment conditions will be analyzed using mixed regression so that all available data are used, and taking into account the dependencies among observations nested within individuals nested within centers. Potential center effects are modeled by including a random effect which enables generalization of results outside the trial and maximizes statistical power [211]. Since group sessions in both treatments are offered in a semi-open format, patients will start with group treatment at different time points. One can imagine that patients starting treatment at the same time point are more interdependent compared to patients starting treatment at different time points. Therefore, we will take into account, if needed, the interdependency of patients. The underlying distributions of the mixed regression models will be determined based on the variable type (i.e., scale or nominal) and the distribution of residuals (e.g., normal, gamma, negative binomial).

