### Sample size

We aim to include 200 participants. Each center intends to recruit at least 18 patients. For the power analysis, we adopted the minimal statistically detectable effect approach [84]. A sample size of 200 will be sufficient to have 80% power to detect moderators of treatment effects that have an effect size of Cohen’s *f* of .20 (small to medium effect size), based on a two-tailed significance level of *p* < .05. In addition, the study has 80% power to detect medium effect-sized (i.e., Cohen’s *f* = .25) moderators of treatment effects, based on a two-tailed significance level of *p* < .01.

Regarding the effectiveness study, with a sample size of *N* = 200 the study is powered at 82% to detect a group difference with a medium effect size of Cohen’s *d* = .50 at a two-tailed significance level of *p* < .05 and assuming a model with center as random effect and an intraclass correlation value of 0.05 corresponding to the center by treatment interaction [85, 86].

Finally, a sample size of *N* = 200 will be sufficient to have 98% power to detect a medium effect size of the mediation effect (*rr* = .09; [87–89]), assuming path *a* (relation between the predictor and mediator) and path *b* (relation between the mediator and outcome measure) both have a medium effect size (*r* = .30), and based on a simplified trivariate mediation model [90].

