### Treatments

#### Format

For patients of both DBT and ST, treatment has a maximum duration of 25 months and starts with a pretreatment phase of approximately four weeks consisting of several (ST: ± three; DBT: ± five) individual sessions in which patients are prepared for the group sessions and become accustomed to their therapists and the treatment model. After the pretreatment phase, patients receive a combined program of individual sessions and group sessions (i.e., treatment phase). Group sessions of both treatments are offered in a semi-open format. If treatment slots are available, new patients can enter the ST group every 10 weeks and for DBT groups at the start of a mindfulness skills module. In DBT, the treatment phase has a maximum duration of 12 months and consists of weekly group sessions (i.e., skills training groups; 150 min), weekly individual psychotherapy sessions (50 min), and between-session consultation. The between-session consultation, often called telephone consultation although all kinds of technology can be used [95], is offered to the patient within limitations set by the individual therapist, varying between access to between-session support within working hours to 24/7 access to between-session support, which is officially the standard in DBT. In ST, the treatment phase has a maximum duration of 18 months consisting of weekly group (90 min) and individual (45 min) psychotherapy sessions for a period of 12 months, continued by weekly group psychotherapy sessions and biweekly individual psychotherapy sessions for a period of six months. Following the treatment phase, patients continue their treatment with a maintenance phase. The maintenance phase of DBT is a recently developed blended aftercare program with a maximum duration of 12 months. The blended aftercare program was developed based on results of previous studies (e.g., [31, 96]) and recommendations by several authors (e.g., [96–98]) to extend the duration of DBT to sustain or even enhance treatment effects. The DBT aftercare program consists of monthly individual psychotherapy sessions, three-monthly group sessions, and an eHealth intervention in which patients have online access to DBT handouts and worksheets [99]. The maintenance phase of ST consists of biweekly individual psychotherapy sessions for a period of three months, continued by three months of one individual session each month. Disregarding the time spent on telephone consultation, homework assignments, and eHealth, and based on 48 working weeks a year, patients will receive about 167 h of treatment if they follow the treatment protocol. Patients who have completed treatment successfully before they reach the maximum number of treatment sessions are allowed to complete treatment earlier, although the assessments will be conducted at the originally planned assessment points. Early termination of treatment requires substantial improvements in the primary and secondary outcomes and is decided in joint decision by the patient and therapist. The treatments are covered by the public health insurance. See Table 2 for an overview of the treatment formats.

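### The effectiveness model omits the centre-by-treatment effect behind the 82% power and ties any further patient dependence, left optional, to start time, so the DBT–ST standard error may be too small

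*Protocol article*

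**What the plan says.** Clinical effectiveness describes a mixed regression "taking into account the dependencies among observations nested within individuals nested within centers". Centre enters as a random effect, and no centre-by-treatment term is named. The section then observes that patients who start together may be more alike than patients who do not, and concludes that "we will take into account, if needed, the interdependency of patients". It gives no criterion for when this is needed.

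Mechanisms of change names the same levels for the mediation models: "repeated measures nested within patients, who in turn are nested within centers".

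Under Format, both arms combine individual sessions with semi-open groups, and "new patients can enter the ST group every 10 weeks". DBT patients can enter at the start of a mindfulness module.

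Under Sample size, "We aim to include 200 participants". For effectiveness, "the study is powered at 82% to detect a group difference with a medium effect size of Cohen’s" *d* = 0.50, "assuming a model with center as random effect and an intraclass correlation value of 0.05 corresponding to the center by treatment interaction".

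The opening of Statistical analyses calls the described methods examples and promises a published update with the selected methods before analysis starts.

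**The concern.** Each patient has an individual therapist and a therapy group, and both appear to belong to one arm of one centre. Differences between therapists or groups then add variance to the arm contrast. A centre intercept cannot absorb this, because it is common to both arms and cancels from their difference.

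The article itself gives reasons to expect such differences. It treats the group and the therapeutic environment as active ingredients, and it says that between-session access varies by centre and by therapist.

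Start time is a poor stand-in for group membership in a semi-open group. The ST treatment phase lasts 18 months, or 78 weeks. Two patients who enter the same ST group 10 weeks apart can share (78 − 10)/78 = 87% of it, if neither stops early, although their start dates differ.

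The sample size calculation already assumes variation of the treatment effect between centres, but the described model does not include it. At stake are confidence intervals that are too narrow and a DBT–ST comparison with more than the nominal 5% false positives. In the mediation models, therapist-level differences in alliance and outcome could be mistaken for a patient-level process.

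**Working it through.** **1. The plan's own figure.** Inputs from Sample size: N = 200, taken as 100 per arm; *d* = 0.50; two-sided 0.05; ICC 0.05. The Design section lists 8 organisations, or 9 sites if the two towns of one organisation count separately.

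- Design effect with J centres: 1 + (200/(2J) − 1) × 0.05. With J = 9 this is 1 + 10.11 × 0.05 = 1.506.
- SE = √(0.02 × 1.506) = 0.1735. Power = Φ(0.50/0.1735 − 1.96) = Φ(0.92) = 82.2%.
- J = 8, 10 and 11 give 80.4%, 83.6% and 84.7%.
- With no clustering, SE = √0.02 = 0.1414 and power is 94.2%.

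The 82% is reproduced, and it already includes clustering within centre and arm. Other definitions of the interaction ICC reach about 82% with 10 or 11 centres, so the exact formula used is not certain.

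**2. What a centre-intercept model does.** Assumptions: 9 centres, 11 patients per centre and arm, one outcome per patient, total variance 1, centre variance 0.05 (which cancels from the contrast), and therapist or group variance ρ nested in centre and arm. The article states neither ρ nor the number of clusters. I used ρ from 0.02 to 0.10 and one to four clusters per centre and arm.

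True SE² = (2/9) × [ρ × S + (0.95 − ρ)/11], where S is the sum of squared cluster sizes divided by 11².

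- Two clusters (5 and 6 patients), ρ = 0.05: S = 61/121 = 0.504; SE² = (2/9)(0.0252 + 0.0818) = 0.0238; SE = 0.154.
- The centre-only model reports 0.138 on average (20,000 simulated trials, no true difference). Ratio 1.12; type I error 2Φ(−1.96/1.12) = 8.0%.
- One cluster, ρ = 0.05: true SE 0.171 against a reported 0.137. Ratio 1.25; type I error 2Φ(−1.96/1.253) = 11.8%.

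| Clusters per centre and arm | ρ = 0.02 | ρ = 0.05 | ρ = 0.10 |
|---|---|---|---|
| 4 | 5.5% (1.02) | 6.2% (1.05) | 7.4% (1.10) |
| 3 | 5.7% (1.03) | 6.8% (1.07) | 8.6% (1.14) |
| 2 | 6.2% (1.05) | 8.0% (1.12) | 11.2% (1.23) |
| 1 | 7.7% (1.11) | 11.8% (1.25) | 18.4% (1.47) |

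Each cell gives the type I error, with the ratio of true to reported SE in brackets. Simulated rejection rates agree to about half a percentage point. At ρ = 0 the rate is 5%.

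**3. With the centre-by-treatment effect fitted.** In the same simulations, a centre-by-treatment random effect tested on J − 1 = 8 degrees of freedom gives type I error between 4.7% and 5.2% for every positive ρ, even with therapist and group left out. Their variance is nested in centre and arm, so the interaction carries it.

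**4. Power if the clustering adds to the assumed interaction.** With clusters of 8 at ICC 0.05, the added design effect is 7 × 0.05 = 0.35. SE = √(0.02 × 1.856) = 0.193, and power is Φ(0.50/0.193 − 1.96) ≈ 74%.

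**The case against.** The strongest reply is that the text is provisional. The methods are called examples, an update is promised, and a full random-effects structure commonly belongs in an analysis plan that is not shown. This stands against a complaint that therapist is merely unlisted. It does not answer the point that the article offers a specific rule built on a poor unit, and that its model does not match its own power assumption.

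A reader might infer that the standard error will certainly be too small. The documents do not support that. It needs a positive therapist or group ICC, which they do not give, and a final model without the interaction named under Sample size. With that term fitted, the error largely disappears.

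A reader might also infer that the optional term would be decided by a low-powered significance test and so usually dropped. The text mentions no test.

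The start-time sentence is graded. It says that patients who start together are more alike, not that others are independent, and it does not commit to clusters defined by start date. So start time is a weak motivation, not a fixed definition. The 87% overlap applies to ST only.

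Finally, the Discussion says that comparing the treatments is not the main aim. That limits the consequence, but comparative effectiveness is still one of four primary objectives. No effect on the treatment selection model has been shown.

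**Conclusion.** The point holds conditionally. If followed as written, the effectiveness model leaves out the centre-by-treatment variation on which the 82% power rests, and it leaves therapist and group dependence optional and loosely defined. Under the assumed ICCs of 0.02 to 0.10, type I error is about 5.5% to 11% with two to four clusters per centre and arm. It is about 12% with one cluster at ICC 0.05, the value that the plan itself assumes for centre by treatment. The one-cluster, ICC 0.10 corner is worse, but the conclusion does not rest on it.

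The figures assume nine balanced centres, one outcome per patient, and therapists and groups nested in centre and arm. For the mediation models the concern is qualitative; no size was computed. This should be settled before analysis and does not threaten the trial's design.

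**What to change.** In the announced protocol update:

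- Clinical effectiveness: include a centre-by-treatment random effect, with small-sample degrees of freedom for the treatment contrast.
- Delete the conditional wording. Define patient dependence by individual therapist and by therapy-group membership with overlapping attendance, not by start date.
- Add therapist or group random effects where they can be separated from centre by arm. Where a centre has a single group per arm they cannot be, and the interaction term carries both.
- Mechanisms of change: account for clustering by therapist.

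The cost is recording therapist and group identifiers with attendance dates, and wider intervals. From the SE alone, the widening runs from a few percent to about 25% (ratios 1.02 to 1.25, leaving out the one-cluster, ICC 0.10 corner). With nine centres, using *t* on 8 degrees of freedom instead of the normal adds a factor of 2.306/1.960 = 1.18. On that basis, the variance behind the stated 82% gives about 71% power (noncentrality 0.50/0.1735 = 2.88), so the update should restate the power for the model chosen.
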